## Abstract

**Background:**

Cardiovascular disease (CVD) remains a leading cause of morbidity and mortality in China. Although the National Basic Public Health Services Program provides annual health checkups for older adults, postscreening management of CVD risk factors such as hypertension, dyslipidemia, and diabetes is often inadequate. The CardioCare system is a digital cardiovascular management platform that integrates risk prediction, personalized health interventions, and continuous engagement to address these gaps.

**Objective:**

This trial aims to evaluate the effectiveness of the CardioCare system in improving triple risk factor control (simultaneous control of blood pressure, lipids, and glycemia) at 12 months among high-risk adults. Secondary objectives include assessing changes in estimated 10-year CVD risk, individual clinical parameters, medication adherence, lifestyle modification, system engagement, usability, satisfaction, and cost-effectiveness.

**Methods:**

This is a single-center, parallel-group, superiority randomized controlled trial with a 1:1 allocation ratio. A total of 300 adults aged ≥50 years with an estimated 10-year CVD risk of >10% and no previous CVD diagnosis will be recruited from the Health Management Center of the First Affiliated Hospital of Sun Yat-sen University in Guangzhou, China. Participants will be randomized to receive either the CardioCare system intervention or minimal usual care for 12 months. The intervention includes risk stratification and communication, weekly personalized SMS text messages or WeChat messages, and cardiologist oversight. The primary outcome is the proportion of participants achieving triple risk factor control at 12 months. Secondary outcomes include clinical, behavioral, usability, and economic measures. Analyses will follow the intention-to-treat principle, with multiple imputation for missing data.

**Results:**

This trial was funded on October 28, 2024. Recruitment is scheduled to begin in January 2026 and conclude in April 2026, with follow-up completed by June 2027. Data analysis will commence in mid-2027, and the main findings are expected to be published by the end of 2027. As of manuscript submission, recruitment has not yet started.

**Conclusions:**

This trial will provide robust evidence on the clinical effectiveness and cost-effectiveness of the CardioCare system in managing multiple cardiovascular risk factors among high-risk adults. The findings will inform the potential for scaling this intervention within health checkup centers and integrating it into national chronic disease management strategies.

## Introduction

The National Basic Public Health Services Program (NBPHSP) in China was launched in 2009 and has greatly improved access to annual health checkups for residents aged ≥65 years. This program aims to improve early detection and management of health issues among older adults, reaching approximately 173 million individuals, which constitutes approximately 12% of the population [1]. These checkups are designed to facilitate the early detection and management of various health conditions, particularly those prevalent in older adults, such as cardiovascular disease (CVD). Despite the extensive reach and potential benefits of this program, postcheckup management of health issues remains suboptimal [2].

Multiple systemic challenges contribute to these deficiencies. The fragmented nature of the health care system often results in poor coordination between primary care providers and specialists, leading to disjointed follow-up and inconsistent treatment [3]. Resource constraints, including shortages of trained personnel and limited funding, further limit the capacity for adequate postcheckup monitoring and support. Low patient engagement is another barrier; many patients fail to adhere to recommended treatments or lifestyle changes, diminishing the effectiveness of follow-up care [4,5]. Moreover, many individuals lack the necessary understanding of their condition and treatment plans, preventing effective self-management. Geographic and economic constraints, long waiting times, and inadequate electronic health record integration contribute to ongoing care fragmentation.

Screening alone is insufficient to improve disease awareness or management [6,7]. Many older adults in China have limited ability to comprehend screening results or the actions required in response [8,9]. Psychological barriers such as fear, denial, or anxiety may further reduce willingness to engage in follow-up care [10]. Infrastructure limitations, high costs, and poor physician-patient communication compound the problem [11,12]. Collectively, these factors underscore the need for a more integrated, patient-centered approach to postscreening management of chronic diseases, particularly CVD.

In light of these persistent challenges (ie, fragmented care, low patient engagement, and insufficient follow-up mechanisms), there is a clear need for innovative, scalable solutions that can support long-term cardiovascular risk management within routine care pathways. The CardioCare system was developed in response to these needs. It integrates an established CVD risk prediction model for risk stratification with personalized digital health management strategies, including tailored reminders, targeted lifestyle and medication interventions, and continuous feedback loops. By delivering individualized guidance and monitoring through a digital platform, the CardioCare system aims to enhance adherence to treatment plans and promote sustained behavior change, thereby improving control of key CVD risk factors. However, whether the implementation of the CardioCare system in routine health checkup services improves CVD management has yet to be examined.

Therefore, we will conduct a randomized controlled trial (RCT) to evaluate the effectiveness of the CardioCare system in improving triple risk factor control, defined as the simultaneous control of blood pressure, lipids, and glycemia, at 12 months among high-risk older adults identified through routine health checkups. Secondary objectives are to (1) assess changes in estimated 10-year CVD risk and individual clinical parameters, including systolic blood pressure (SBP), low-density lipoprotein cholesterol (LDL-C), and glycated hemoglobin (HbA_1c_); (2) evaluate medication adherence, adoption of lifestyle modifications, and patient engagement with the system; (3) assess system usability and satisfaction among participants and health care providers; and (4) examine the potential cost-effectiveness of the intervention compared with minimal usual care.

## Methods

### Participants

This single-center, 2-arm, parallel-group RCT with a 1:1 allocation ratio will be conducted at the Health Management Center of the First Affiliated Hospital of Sun Yat-sen University in Guangzhou, China (Figure 1). The trial is designed within a superiority framework to determine whether the CardioCare system is more effective than minimal usual care in achieving triple risk factor control at 12 months among high-risk adults.

**Figure 1. F1:**
[figure not shown]
Study flowchart. CVD: cardiovascular disease.

Eligible participants will be aged ≥50 years, have an estimated 10-year CVD risk greater than 10% calculated using the Guangzhou Biobank Cohort Study (GBCS) model [13], have no previous diagnosis of CVD, and own a mobile device capable of receiving messages from the CardioCare system. The GBCS model has been validated in a large urban Chinese cohort and is appropriate for identifying high-risk individuals in this population [13]. Participants must reside in Guangzhou for the duration of the study and provide written informed consent. Individuals will be excluded if they have severe comorbidities that preclude regular follow-up in the judgment of a study clinician based on medical record review, a life expectancy of less than 1 year, recent participation in similar CVD management programs, or any other condition judged by the investigators to interfere with safe participation.

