### Random Allocation and Allocation Concealment

A statistician not involved in participant recruitment will generate the random allocation sequence using computer-generated random numbers. Randomization will be stratified by sex, with random block sizes ranging from 4 to 12 undisclosed to the recruitment team to ensure unpredictability. Allocation concealment will be maintained using sequentially numbered opaque, sealed envelopes prepared by staff independent of the enrollment process.

Research assistants will identify eligible participants, send invitations, and obtain informed consent, after which the next available envelope will be opened to reveal allocation. Personnel enrolling participants will not have access to the allocation sequence.

Participants and care providers will not be blinded due to the nature of the intervention. Outcome assessors and statisticians will remain blinded to allocation. Group codes will be masked during analysis, and the randomization key will only be revealed after the primary analysis is completed. No emergency unblinding procedures are required given the nonpharmacological nature of the intervention.

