### Outcomes

The primary outcome is the proportion of participants achieving simultaneous control of blood pressure, lipids, and glycemia at 12 months, defined as SBP of <130 mm Hg and diastolic blood pressure of <80 mm Hg, LDL-C of <2.6 mmol/L, fasting plasma glucose of <7.0 mmol/L, and HbA_1c_ of <7% (Table 1). Secondary outcomes include (1) clinical measures (changes in estimated 10-year CVD risk [GBCS model]; mean changes in SBP, LDL-C, triglycerides, fasting plasma glucose, and HbA_1c_; and the proportion achieving control of individual risk factors at 12 months), (2) behavioral measures (medication adherence and adoption of lifestyle modifications), (3) system-level outcomes (participant engagement with the CardioCare system and usability and satisfaction among participants and physicians), and (4) economic outcomes (incremental cost-effectiveness expressed as cost per participant achieving triple risk factor control and per quality-adjusted life year [QALY] gained; Table 1).

Medication adherence and lifestyle modifications (diet, physical activity, and smoking) will be assessed using structured questionnaires adapted from previously validated tools applied in chronic disease studies in Chinese populations. Measurements for all primary and secondary outcomes will be taken at baseline and 6 and 12 months after enrollment. To assess feasibility and acceptability, we will evaluate (1) recruitment rate (participants enrolled and approached); (2) retention rate at 12 months; (3) system engagement metrics, including number of messages opened and responded to; and (4) participant-reported usability and satisfaction at 12 months. Usability will be assessed using the System Usability Scale, and satisfaction will be measured using a 5-point Likert scale. These data will inform scalability potential and guide future implementation strategies. Quantitative feasibility metrics will be summarized descriptively, and comparisons between groups will be exploratory.

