### Sample Size Estimation

The sample size was calculated to detect an absolute difference of 15 percentage points in the primary outcome (ie, 20% in the control group vs 35% in the intervention group), with 80% power and a 2-sided α of .05. This requires 126 participants per arm. Allowing for 15% attrition, the final target sample size is 300 participants (150 per group). This expected difference is based on previous studies in Chinese older adult populations showing triple risk factor control rates ranging from 15% to 25% under usual care and on effect sizes from similar multicomponent digital interventions, which have reported 10– to 20–percentage point improvements in risk factor control [14]. Recruitment will take place during routine health checkup visits, with eligible individuals identified from their health data and approached in person by a trained research assistant. Additional recruitment will be supported through study posters in the Health Management Center and announcements on the hospital’s WeChat platform.

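### Baseline triple control is measured and probably strongly prognostic, but neither the randomisation strata nor the primary analysis uses it

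*Protocol article*

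**What the plan says.** Eligibility (Protocol article, Methods, Participants) rests on age, no previous CVD, a mobile device, residence in Guangzhou, consent, and a requirement to "have an estimated 10-year CVD risk greater than 10% calculated using the Guangzhou Biobank Cohort Study (GBCS) model". The exclusions cover severe comorbidity and "a life expectancy of less than 1 year, recent participation in similar CVD management programs, or any other condition judged by the investigators". None of these refers to whether a risk factor is on or off target.

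The endpoint is a status at one time point, not a change: "The primary outcome is the proportion of participants achieving simultaneous control of blood pressure, lipids, and glycemia at 12 months" (Outcomes). Its components are measured at baseline as well as at 6 and 12 months (Outcomes; Data Collection and Management), and Table 2 also ticks laboratory tests and blood pressure in the enrolment window before randomisation.

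On allocation, "Randomization will be stratified by sex"; no other stratification factor is named (Random Allocation and Allocation Concealment). The Statistical Analysis section compares the primary outcome by a chi-square test with a risk difference and 95% CI. Adjustment for baseline values is stated only for the continuous secondary outcomes.

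The trial is sized on "20% in the control group vs 35% in the intervention group", "with 80% power and a 2-sided α of .05", and the usual-care rate is supported by earlier studies reporting "triple risk factor control rates ranging from 15% to 25% under usual care" (Sample Size Estimation). That section does not say whether these rates describe everyone enrolled or only people off target at entry.

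**The concern.** Someone at all targets at entry cannot move from uncontrolled to controlled; the only question for that person is whether control is kept. Someone off target has to gain it. The two groups probably have very different chances of being controlled at 12 months whatever the arm, which makes baseline triple control a natural candidate for the strongest single predictor of the primary outcome.

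Two things follow when such a variable is left out of both the strata and the analysis. The variation between the two groups stays in the standard error, so the trial has less power than its data could give. And if one arm happens to receive more participants who start controlled, the unadjusted risk difference moves with that imbalance. Stratifying by sex alone does not prevent this.

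**Working it through.** **The plan's own figure.** For 20% vs 35%, two-sided α 0.05 and 80% power, the pooled formula is n = [1.96·√(2·0.275·0.725) + 0.8416·√(0.20·0.80 + 0.35·0.65)]² / 0.15² = (1.2377 + 0.5239)² / 0.0225 ≈ 138 per arm. The stated 126 does not reproduce; it gives 76.3% power. That is a separate matter, and the point here does not depend on it. After 15% attrition, 150 per arm leaves 127.5, so 127 per arm is used below.

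**Assumptions.** The documents give neither the share controlled at baseline (q) nor the proportion of those people still controlled at 12 months without the intervention (s). I take q = 20% and s = 50–70%. To keep the plan's overall control-arm rate of 20%, the rate among the others is c = (0.20 − q·s)/(1 − q), which is 12.5%, 10% and 7.5% for s = 50%, 60% and 70%.

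**Chance imbalance.** The SD of the between-arm difference in baseline control is √(2·q·(1−q)/n) = √(2·0.20·0.80/150) = 4.6 points. With s = 60% and c = 10%, the shift in the risk difference is 4.6 × (0.60 − 0.10) = 2.3 points per SD. Holding that 50-point gap, q = 10% gives an SD of 3.5 and a shift of 1.7 points; q = 25% gives 5.0 and 2.5.

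**Precision.** Unadjusted, n·Var = p₀(1−p₀) + p₁(1−p₁). Adjusted, each term becomes q·s(1−s) + (1−q)·c(1−c) with that arm's own rates. Power is Φ(D/√Var − 1.96) at 127 per arm.

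*15 points in both groups, 15 overall.* Unadjusted n·Var = 0.1600 + 0.2275 = 0.3875; power 78%.

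| s | adjusted n·Var | variance cut | power |
|---|---|---|---|
| 50% | 0.1375 + 0.2050 = 0.3425 | 12% | 82% |
| 60% | 0.1200 + 0.1875 = 0.3075 | 21% | 86% |
| 70% | 0.0975 + 0.1650 = 0.2625 | 32% | 91% |

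*15 points only in those off target, 12 overall.* Unadjusted n·Var = 0.1600 + 0.2176 = 0.3776; power 60%.

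| s | adjusted n·Var | variance cut | power |
|---|---|---|---|
| 50% | 0.1375 + 0.2095 = 0.3470 | 8% | 63% |
| 60% | 0.1200 + 0.1980 = 0.3180 | 16% | 67% |
| 70% | 0.0975 + 0.1815 = 0.2790 | 26% | 73% |

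These use the unpooled variance; the pooled test gives about 77% and 59% unadjusted. If the baseline mix is itself treated as sampled, the second table gains a term of 0.20·0.80·0.15²/2 = 0.0018, which lowers the cuts by about half a point.

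**Is the planned effect diluted?** If the intervention raises retention among controlled participants by g points and control among the others by 15, the overall effect is q·g + (1−q)·15. With q = 20% and g = 0, 5, 10 and 15, this is 12, 13, 14 and 15 points, with pooled power of 59%, 65%, 71% and 77% at 127 per arm. With g = 0 and q from 10% to 25%, the effect is 13.5 to 11.25 points and power 68% to 54%. The result turns on g and q, and the documents give neither.

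**Would restricting entry raise power?** Among people off target the control rate would be 7.5–12.5%. If the 15-point difference holds there, power at 127 per arm is 92–85%. If instead the plan's odds ratio holds, (0.35/0.65)/(0.20/0.80) = 2.15, the difference is 7.4–11.0 points and power 46–63%.

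**The case against.** The strongest reply is that randomisation keeps the unadjusted chi-square valid: its standard error already allows for chance imbalance, so there is no bias to correct. That stands. The point is about efficiency and about how well one realised estimate can be trusted, not about validity.

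A second reply is that covariates are commonly left to an analysis plan, which is not shown. This has some force, but the article does name the primary test and reserves baseline adjustment for other outcomes, and a stratification factor cannot be added in an analysis plan once randomisation has begun.

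A third reply is that entry by risk score is a legitimate choice for a trial of a system meant for routine checkup services. That also stands.

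Two stronger readings are tempting. A reader might infer that controlled participants cannot gain on the endpoint and so must dilute the effect for which the trial is sized. The documents do not support this. The outcome is status at 12 months, so the intervention can make a difference by maintaining control. The 20% and 35% are stated for whole arms and may already include controlled people. The 15–25% range comes from older Chinese adults in earlier studies, not specifically from adults above the 10% risk threshold. Nor are the risk model's inputs given, so how often a qualifying score goes with all factors at target is unknown.

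A reader might also infer that entry must be limited to people with a factor off target. The power gain from that depends wholly on holding the 15-point difference at a lower control rate; under the plan's odds ratio it is not shown.

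**Conclusion.** The concern holds as a missed gain in precision. Participants at all targets may enrol and have limited room to benefit, and the variable that identifies them is collected but used in neither strata nor primary analysis. With 20% controlled at baseline and 50–70% retention, both assumed, using it cuts the variance of the risk difference by about 8–32%. Power at 127 per arm rises from about 78% to 82–91% for a 15-point overall effect, or from 60% to 63–73% for 12 points. The gain shrinks if few participants start controlled or if baseline control predicts the outcome weakly.

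Dilution remains possible but unshown, because the sample size section does not identify the population behind its rates. That ambiguity should be resolved in its own right.

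**What to change.** Before recruitment opens:

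- Keep the eligible population and stratify randomisation by baseline triple control (yes/no) as well as sex.
- Make the primary analysis a risk difference with 95% CI adjusted for baseline triple control and sex, for example by standardisation from a logistic model or by Mantel-Haenszel weighting. Keep the chi-square test as a sensitivity analysis.
- Define baseline control by the same components as the endpoint. The Outcomes text includes fasting plasma glucose ("SBP of <130 mm Hg and diastolic blood pressure of <80 mm Hg, LDL-C of <2.6 mmol/L, fasting plasma glucose of <7.0 mmol/L") and Table 1 leaves it out of the primary outcome definition, so that has to be settled first.
- State in Sample Size Estimation whether 20% vs 35% describes all enrolled participants or only those off target at entry, and give the expected share at target.

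The cost is one more stratification factor (four envelope series instead of two), baseline results in hand before the envelope is opened, and slightly more analysis work. Nobody becomes ineligible.

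Limiting entry to people with at least one factor off target is an option for the sponsor, not a required correction. It changes the target population, needs a new control-arm rate, and is not shown to raise power.

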### Random Allocation and Allocation Concealment

A statistician not involved in participant recruitment will generate the random allocation sequence using computer-generated random numbers. Randomization will be stratified by sex, with random block sizes ranging from 4 to 12 undisclosed to the recruitment team to ensure unpredictability. Allocation concealment will be maintained using sequentially numbered opaque, sealed envelopes prepared by staff independent of the enrollment process.

Research assistants will identify eligible participants, send invitations, and obtain informed consent, after which the next available envelope will be opened to reveal allocation. Personnel enrolling participants will not have access to the allocation sequence.

Participants and care providers will not be blinded due to the nature of the intervention. Outcome assessors and statisticians will remain blinded to allocation. Group codes will be masked during analysis, and the randomization key will only be revealed after the primary analysis is completed. No emergency unblinding procedures are required given the nonpharmacological nature of the intervention.

### Intervention and Control

The CardioCare system uses a structured message-tailoring algorithm that integrates clinical data, participant risk profiles, and previous engagement records to personalize message content and frequency. Cardiologists oversee message template development and conduct monthly reviews to ensure clinical relevance and appropriateness. Participant engagement is continuously monitored through automated system logs, which record message delivery and interaction. Predefined engagement thresholds trigger alerts to research staff for follow-up support. This operational framework follows the Template for Intervention Description and Replication guidance for intervention specification, ensuring reproducibility and transparency in intervention delivery.

The intervention group will receive a personalized intervention from the CardioCare system for 12 months. This system integrates CVD risk stratification using the GBCS model with tailored weekly SMS text messages or WeChat messages covering medication adherence, diet, exercise, and follow-up reminders. Messages will be reviewed by a cardiologist before dispatch and customized based on each participant’s clinical profile and previous engagement. Message types will vary in intensity and content (eg, motivational, educational, or reminder based) depending on previous adherence and risk level. All messages are logged automatically, and participant engagement (eg, message reads, replies, and link clicks) is continuously monitored. Participants with declining engagement will be flagged for follow-up by the research assistant team, ensuring responsiveness. Cardiologist review takes place monthly or upon significant clinical change using an internal dashboard linked to participant records.

The control group will receive minimal usual care, consisting of notification of health checkup results and general recommendations to seek outpatient follow-up if indicated. After completing the 12-month follow-up, control group participants will be offered access to the CardioCare system. Participants may discontinue the intervention at any time or if advised by the study physician. No restrictions will be placed on concomitant medical care.

